### Data handling

The Parker Institute’s statistical unit handles all data-management procedures and the trial central databases (SQL Server 2008 Express; Microsoft). The user-friendly touch screen interface obtains all self-reported outcome questionnaire measures from which all data are transferred directly to the study database [25]. During the intervention phase only the database manager from the statistical unit at the Department of Rheumatology has access to the database. Paper-based forms will only be used in case of server breakdown and the subsequent data entry will be performed by personnel not involved in the intervention. Research records and data collection are obtained according to the Danish Personal Data Act (DPA) guidelines and recommendations given in their study approval (DPA approval number 2014-41-2673).

The local ethical committee and an external advisory board at the Parker Institute will ensure patient safety and the highest possible data quality. According to Danish law, independent physicians from the local ethical committee and/or the National Health and Medicine Authorities can conduct monitoring visits on a regular basis.

### Statistics

Data analyses will be performed using the SAS System for Windows (Release 9.3, SAS Institute Inc., Cary, NC, USA). Descriptive statistics of participant baseline characteristics will be presented for both groups to assess their comparability. Continuous data will be analysed using an Analysis of Covariance (ANCOVA), with a factor for Group, using the baseline value as a covariate to reduce the random variation and increase the statistical power. Unless stated otherwise, results will be expressed as the difference between the group means with 95% confidence intervals (CIs) based on a General Linear Model (GLM) procedure. *P*-values will only be reported if appropriate. We will attempt to follow up all randomised participants, even if they withdraw from allocated treatment. The main analyses will be on sick leave after 6 months where participants will be analysed according to the allocated group. The Cox proportional hazard model will be used to analyse differences in time until return to work, including the intervention group as the only independent variable.

The cost-effectiveness analysis of our occupational medicine intervention will include predictors of return to work, based on questionnaire outcomes, the MRI evaluation and clinical examination. This study is testing an additional intervention to the treatment provided by the participants’ GP; therefore, the direct intervention costs included the costs of the workplace and our occupational medicine intervention. This will be compared to the costs of production losses estimated by a price of production loss of a worker per day. Further direct non-health care costs will be included (such as pension expenses, loss of productivity, schooling and redeployment).

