### Sample size

For a two-sample pooled *t*-test of a normal mean difference with a two-sided significance level of 0.05 (*P* < 0.05), assuming a common standard deviation of 17 days [17,34], a sample size of 127 participants per group is required to obtain a power of at least 80% to detect a mean difference of 6 days. Expecting some drop-outs during the trial period (less than 20%), it was decided for pragmatic reasons to enrol 300 participants in total (that is, 150 participants in each group). Including 300 participants in the intention-to-treat population, based on the assumptions above, corresponds to a statistical power of 86.1% to detect a mean difference of 6 days.

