### Randomisation

The allocation occurs through a 1:1 ratio by a predetermined restricted randomisation scheme. The participants are stratified according to their age at enrolment (<40 years or ≥ 40 years) and gender (male or female). The eligible participants are randomly assigned in permuted blocks of 4 and 6, according to computer-generated random numbers, to be enrolled in either the intervention or control group. The randomisation is administered by predetermined sequentially numbered, opaque envelopes stored in a locked cabinet in a secure location. The randomisation is administered by Good Clinical Practice (GCP)-trained personnel not involved in the outcome measurement or the intervention.

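### Allocation is stratified by age group and gender, but the ANCOVA as listed leaves both out and the Cox model excludes them, so tests are conservative if these factors are prognostic

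*Protocol article*

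**What the plan says.** Under Randomisation: "The participants are stratified according to their age at enrolment", cut at 40 years, and to gender, which gives four strata. Allocation is 1:1, with participants "randomly assigned in permuted blocks of 4 and 6".

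Under Statistics, continuous data are analysed by ANCOVA "with a factor for Group, using the baseline value as a covariate". The stated reason for the covariate is less random variation and more power. Group differences with 95% confidence intervals are the main reported result. Time until return to work is analysed by a Cox model "including the intervention group as the only independent variable".

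The protocol article nowhere names age group or gender as a model term. The two sentences differ in force: the ANCOVA sentence lists its terms without these factors, while the Cox sentence rules out anything except group.

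**The concern.** Stratified permuted blocks make the arms nearly identical in age group and gender. If those factors are prognostic, this lowers the true variance of the estimated treatment difference. A model without the factors does not see the reduction: their variance stays in the residual, so the reported standard error is larger than the true one. Confidence intervals come out too wide and the test rejects less often than 5% under the null.

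The stake is modest but real. The protocol reports mainly by confidence interval, and it already justifies one covariate on grounds of precision. The same argument applies to the two factors that were thought important enough to stratify on.

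**Working it through.** **Inputs from the Sample size section.** The calculation is for a "two-sample pooled *t*-test of a normal mean difference with a two-sided significance level of 0.05", "assuming a common standard deviation of 17 days", with a difference of 6 days, 127 per group for at least 80% power, and 86.1% power at 150 per group.

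**The plan's own figures.** With the noncentral t distribution, power is 80.0% at 127 per group and 86.1% at 150 per group. Both stated figures reproduce.

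**Assumed input.** Let R² be the share of outcome variance that age group and gender explain beyond the terms already in the model. The documents give no value, so I take 0%, 2%, 5% and 10%. The 17 days are treated as the standard deviation before the strata are added.

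**Linear model, 150 per group.**

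- Reported SE without strata: S0 = 17 × √(2/150) = 1.963 days, whatever R² is.
- True SE under stratified allocation: S = S0 × √(1 − R²).
- Overstatement: 1/√(1 − R²) − 1.
- Actual type I error of the unadjusted test: 2 × [1 − Φ(1.96/√(1 − R²))].
- Power of the unadjusted test: Φ((6 − 1.96 × S0)/S).
- Power of the adjusted test: Φ(6/S − 1.96).

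| R² | True SE (days) | SE overstated by | Type I error | Power, unadjusted | Power, adjusted | Gain (points) |
|---|---|---|---|---|---|---|
| 0% | 1.963 | 0% | 5.0% | 86.4% | 86.4% | 0 |
| 2% | 1.943 | 1.0% | 4.8% | 86.6% | 87.0% | 0.4 |
| 5% | 1.913 | 2.6% | 4.4% | 87.0% | 88.0% | 1.0 |
| 10% | 1.862 | 5.4% | 3.9% | 87.6% | 89.7% | 2.0 |

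Powers here use the normal approximation, which is why the first row shows 86.4% where the t calculation gives 86.1%.

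**Simulation check.** 300 participants in four strata, permuted blocks of 4 and 6, no baseline covariate, 6000 runs per setting. Monte Carlo error on a 5% rate is √(0.05 × 0.95/6000) = 0.3 points.

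- R² 5%: type I error without strata 4.2%; power 86.5% without and 87.5% with strata.
- R² 10%: type I error without strata 3.8%; power 87.2% without and 89.4% with strata.
- The estimated difference averaged 6.0 days with and without strata in every setting with a true difference of 6 days, so there is no bias.

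**Cox model.** Simulated with follow-up cut at 182 days, 1500 runs, assumed hazard ratio 1.4 (log 0.336) and an assumed log hazard ratio for each factor. Monte Carlo error on a 5% rate is 0.6 points.

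| Log HR per factor | Mean log HR for group, unadjusted / adjusted | Power, unadjusted / adjusted | Type I error, unadjusted / adjusted |
|---|---|---|---|
| 0 | 0.341 / 0.343 | 79.5% / 79.3% | 4.7% / 4.7% |
| 0.3 | 0.327 / 0.340 | 76.8% / 79.7% | 4.9% / 5.3% |
| 0.6 | 0.307 / 0.346 | 72.7% / 80.5% | 3.7% / 4.7% |

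At 0.6 per factor and hazard ratio 1.4, the unadjusted model reports an SE of 0.123 while the estimate varies with an SE of 0.114. The adjusted model also reports 0.123. Adjustment here does not shrink the reported SE; it brings type I error close to nominal and recovers the power.

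**The case against.** The best case against runs as follows. This is a condensed article, the analysis plan is not shown, and further covariates are commonly settled there. The ANCOVA sentence does not say that its list is complete. The explicit restriction sits on the Cox model, which is not the primary analysis. The effect exists only if the factors are prognostic beyond baseline sick leave, and no figure is given for that.

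Much of this stands. The ANCOVA limb is weaker than the Cox limb, the size is conditional, and the error is on the safe side. What does not stand is that silence disposes of the point. The Cox sentence is not silent, so an analysis plan that added the strata there would contradict it. The ANCOVA as listed gives a conservative standard error whenever the factors matter.

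A reader might infer more than the documents support:

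- **That power rises from 86.1% to 86.8%, 87.8% or 89.5%.** These are the adjusted powers by the t calculation, but 86.1% is the wrong comparator. With prognostic strata, the unadjusted test under stratified allocation already has more power than that, so the gain is smaller.
- **That the benefit of stratifying is lost.** Balance and the smaller true variance come from the allocation itself. What is lost is their reflection in the reported SE.
- **That the Cox hazard ratio is simply biased towards 1.** Hazard ratios are non-collapsible: the unadjusted and adjusted models estimate a marginal and a conditional quantity, which differ when the factors are prognostic.
- **That the result or the sample size is unsafe.** The ANCOVA estimate is unbiased, type I error is not inflated, and the stated sample size reproduces.

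**Conclusion.** The point holds as a mismatch between design and analysis, firmly for the Cox model and as written for the ANCOVA. Its consequence is a conservative test and over-wide intervals, with no bias in the ANCOVA. For the primary comparison the loss is small: within the assumed R² range of 2% to 10%, about 0.4 to 2 points of power and an SE 1% to 5% too large, and none at R² = 0. The Cox loss can be larger, about 3 to 8 points in the two simulated cases with prognostic factors, but that rests entirely on assumed hazard ratios. The change is worth making because it costs almost nothing and makes the analysis follow the allocation, not because the trial's conclusions are at risk without it.

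**What to change.** In the Statistics section, or in the analysis plan with a matching correction to the protocol:

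- Add age group (under 40, or 40 and over) and gender as fixed factors to the ANCOVA of six-month sick leave and of the other continuous outcomes, alongside group and the baseline value.
- Include both in the Cox model as covariates or as strata, and delete the clause "including the intervention group as the only independent variable". State that the resulting hazard ratio is conditional on these factors.

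The cost is wording plus two degrees of freedom (main effects) or three (all four strata) out of 300 participants. No extra data are needed, since both variables must be known before a participant can be allocated. Recruitment was still open when the article was submitted. The terms should be fixed before any unblinded results are seen, so that no choice between adjusted and unadjusted results arises afterwards.

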The objective of this study is to evaluate whether an additional occupational medicine intervention with focus on early workplace oriented counselling and workplace intervention can retain individuals with physically demanding jobs and LBP in employment. The secondary aims are to identify prognostic factors for success of this occupational medicine intervention using the baseline outcomes: pain level, health status, fear avoidance behaviours, job satisfaction, work ability, and degenerative magnetic resonance imaging (MRI) findings. Among these variables, we aim to identify individuals who already have a good prognosis and therefore have no need for this larger scale intervention. Later, a cost-benefit analysis of the intervention will be performed.

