### Inclusion criteria

Eligible participants are persons between 18 and 65 years of age with a current episode of 2 to 4 weeks of LBP with a self-reported physically demanding job, who independently of sick leave status, express concerns about the ability to maintain their current job. They must be able to speak, read and understand Danish in such a way that they can give informed consent for participating. The potential participants have to be in employment for at last 30 hours/week and must accept workplace visits by an occupational physician (OP) or physiotherapist. According to Robreok *et al*. [24], physically demanding work is defined by a self-reported patient statement using a single question: *Would you strongly agree, agree, disagree or strongly disagree that your work is physically demanding?* Those individuals who strongly agree or agree are considered to have physically demanding work. LBP is defined as pain located in the lower back with or without radiating symptoms and must fulfil International Classification of Diseases, 10th Revision (ICD-10) back pain codes: DM43.1; DM47; DM48.0; DM54.3-54.9; DM 51.1; DM51.2; DM51.3; DM 51.9; DM53.8; DM53.9. [http://apps.who.int/classifications/icd10/browse/2010/en].

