### Primary outcome

The primary outcome of this study is retention at work after occupational medicine intervention, measured as the accumulated duration of self-assessed sick leave due to LBP over three and six months. The sick leave data is assessed weekly on a paper-based sick leave diary. The participants have to answer the following question: *How many days have you been on sick leave due to LBP during the past week?* For the first six months, all participants will weekly receive a text message with a reminder to answer the sick leave question in the diary. Additional participants can be contacted by telephone every second week, and the accumulated sick leave will be registered by an independent observer.

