### Secondary outcomes

Secondary outcomes will focus on sick leave and different aspects associated with LBP with the potential to affect the ability to return to/stay at work. Sick leave is additionally assessed by using data from the Danish National Register on Public Transfer Payments (Danish acronym DREAM). The DREAM register includes week-by-week records of any type of public transfer payment at an individual level. Sick leave periods of less than two consecutive weeks are not recorded in the DREAM register. Pain will be evaluated by using the 13-item painDETECT questionnaire, which includes measurements of LBP on an ordinal 11-point numerical rating scale (NRS: 0 = no LBP; 10 = worst LBP possible) [26]. The validated 24-item Roland Morris Disability Questionnaire will measure participant-rated LBP disability [27]. The participant’s work ability will be rated by three selected questions from the seven-item Work Ability Index questionnaire [28] and by an occupational standard baseline questionnaire collecting information on demographics, education level, leisure-time physical activity and the psychosocial work environment. General health status is collected with the Short Form Health Survey (SF-36) to assess changes in physical functional (SF-36 physical function subscale) and mental health (SF-36 mental health subscale) [29,30]. The psychosocial aspect of LBP will be measured with the validated Fear Avoidance Beliefs Questionnaire, a 16-item instrument measuring back-pain fears on two subscales related to physical activity and work which are rated from 0 (completely disagree) to 6 (completely agree) [31] [http://fysio.dk/fafo/Nyheder/Fear-Avoidance-Beliefs-Questionnaire]. Overall satisfaction with the intervention for the participants of this group is rated at each follow-up visit on an 11-point NRS with the anchors ‘not at all satisfied’ to ‘extremely satisfied’. The baseline MRI evaluation represents a descriptive outcome, and the lumbar degeneration is measured as a sum score of the discus at all lumbar levels [32,33].

If a participant is unable to attend the half-year visit in person, the primary outcome measures and a subset of secondary outcomes can be administered via paper-based questionnaires sent to the participant’s home with a stamped return envelope. All primary and secondary outcome assessments are also presented in Table 1.

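### The Cox model for time to return to work names no risk set, although participants enrol whether or not they are on sick leave

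*Protocol article*

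**What the plan says.** The Statistics section gives the time-to-event analysis one sentence: "The Cox proportional hazard model will be used to analyse differences in time until return to work". Group is to be the sole covariate. The section gives no analysis set, time origin, event definition or censoring rule for this model.

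The Inclusion criteria require employment ("The potential participants have to be in employment for at last 30 hours/week") and admit people who, "independently of sick leave status, express concerns about the ability to maintain their current job". Participants may therefore be at work or on leave when randomised. This matches the aim in the Background, which is to find out whether the intervention "can retain individuals with physically demanding jobs and LBP in employment".

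The primary outcome is accumulated sick leave due to low back pain, taken from a weekly diary question: "How many days have you been on sick leave due to LBP during the past week". Time to return to work is not among the outcomes in the Primary outcome section, the Secondary outcomes section or Table 1. The register used as a second source of sick-leave data has a floor: "Sick leave periods of less than two consecutive weeks are not recorded in the DREAM register". Randomisation is stratified by age group and gender, not by sick-leave status.

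**The concern.** Return to work has a meaning only for someone who is absent. A participant who is at work at randomisation and never goes on leave has no such time. The model cannot be run on all randomised participants without a choice that the article does not state: enter these people as events at time zero, censor them, drop them, or start the clock at a later absence.

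The choices answer different questions. An event at time zero records a state that existed before treatment and carries no information about the intervention. Starting the clock at a later absence compares only those who went on leave after randomisation. The intervention aims to prevent exactly that, so the two arms' absentees need no longer be comparable. What is at stake is a published between-group hazard ratio that may not reflect the randomised comparison.

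**Working it through.** **1. The plan's own figures.** The only stated power figures concern the primary outcome: SD 17 days, difference 6 days, two-sided 0.05. The normal formula gives n = 2 × (1.960 + 0.842)² × 17² / 6² ≈ 126.0, which rounds up to 127 per group. The exact t-test power is 80.0% at 127 and 86.1% at 150 per group. Both stated figures reproduce. No figure is given for the Cox model.

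**2. The sections side by side.** Inclusion criteria: sick-leave status is not a condition of entry. Statistics: a between-group model for return to work, with no restriction to those on leave. Outcome sections and Table 1: no return-to-work definition that would settle who is at risk. So a valid risk set may be intended, but none is stated.

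**3. What happens if spells that start after randomisation are used.** All inputs here are assumptions. Take participants at work at baseline. In controls, 25% have a short spell (exponential, mean 5 days) and 15% a long one (exponential, mean 40 days), censored at 182 days. The intervention prevents some spells and does not change the length of the rest.

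Mean days per participant:
- Control: 0.25 × 5 + 0.15 × 40 × (1 − e^(−182/40)) = 1.25 + 5.94 = 7.19.
- 60% of short spells prevented: 0.10 × 5 + 5.94 = 6.44.
- 30% of short spells prevented: 0.175 × 5 + 5.94 = 6.81.

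Simulated Cox hazard ratios for return to work among those who start leave (ranges are across repeated runs):

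| Spells prevented | Hazard ratio |
|---|---|
| 60% of short, no long | 0.75 to 0.79 |
| 30% of short, no long | 0.87 to 0.90 |
| 30% of short, 30% of long | about 1.0 |
| 20% of short, 50% of long | 1.14 to 1.16 |

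The intervention reduces sick leave in every row, yet the hazard ratio falls below, at or above 1 according to which spells are removed.

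**4. A second mechanism.** Here an unobserved severity drives both the risk of new leave (set at 40% in control and 20% in intervention for average severity) and a slower return, with no true effect on speed of return. The assumed share on leave at baseline was 25%, 50% or 75%. The hazard ratio was 0.88 to 0.91 among those with new leave only, and 0.98 to 1.01 among those on leave at baseline. Pooling everyone ever on leave gave 0.98 to 1.02, because two opposing selections happened to offset each other in this set-up.

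**5. Precision after restriction to those on leave at randomisation.** Let f be the share on leave, which the article does not give. There are then at most D = 300f events. Schoenfeld power is Φ(|ln HR| × √D / 2 − 1.96). For example, with HR 1.5 and D = 150: 0.405 × 12.25 / 2 − 1.96 = 0.52, so power is 70%.

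| f | Maximum events | Power, HR 1.4 | Power, HR 1.5 |
|---|---|---|---|
| 0.25 | 75 | 31% | 42% |
| 0.50 | 150 | 54% | 70% |
| 0.75 | 225 | 71% | 86% |
| 1.00 | 300 | 83% | 94% |

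The hazard ratios of 1.4 and 1.5 are assumptions for scale.

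**The case against.** The strongest reply is that returning to work presupposes absence, so limiting the model to participants absent at baseline is an ordinary reading of the sentence. Baseline questionnaires cover sickness absence, so the information may already be collected. Analysis set, origin and censoring for a supporting model usually belong in an analysis plan, which is not shown. The phrase "participants will be analysed according to the allocated group" belongs to the main sick-leave analysis and does not say that the Cox model takes in everyone.

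Much of this stands. A reader might infer that mixed enrolment leaves no valid risk set at all. It does not, because those on leave at randomisation form one. A reader might also infer that the model will point to harm when the intervention helps. The article nowhere says that later spells will be used, and the illustrations show that the direction depends on the assumed pattern of prevention. Nor is week-level timing an error: a Cox model with tie handling copes, and rounding to weeks left the simulated hazard ratios broadly unchanged.

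What the reply does not remove is the mismatch within the article. It commits to a named between-group analysis whose endpoint its own eligibility rule leaves undefined for some participants, and nothing else in the text settles which reading applies.

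**Conclusion.** The concern holds as a failure to specify. The return-to-work model has no stated risk set in a trial that enrols people both at work and on leave, and at least one open reading would break the randomised comparison. The possible distortion cannot be sized from the article. Under the assumed patterns the hazard ratio ran from about 0.75 to about 1.16 with no true effect on speed of return. These figures show sensitivity and do not predict a result.

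It would be wrong to conclude that the trial's main result is in doubt. Accumulated sick-leave days are defined for every participant, the sample size rests on them, and the article names sick leave after 6 months as its main analysis. This is a correction that should be made to a supporting analysis, not a threat to the primary conclusion.

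**What to change.** State the following before the data are analysed:

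- **Population:** the return-to-work Cox model covers participants on sick leave due to low back pain at randomisation. This is a baseline characteristic, so the randomised comparison is kept within the subset. Confirm that the baseline questionnaire records current status as well as past days.
- **Origin, event and censoring:** time zero at randomisation; a defined return-to-work event from the weekly diary, for example the first diary week with zero sick-leave days; time in weeks with tie handling; censoring at 6 months.
- **Exclusion:** spells that begin after randomisation are not used as return-to-work times.
- **Covariates:** add the stratification factors, age group and gender, to the model, which is now limited to group alone.

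Time to first sick-leave week among those at work at baseline is an optional extra. It would be a new endpoint, not a repair of this one.

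The cost is wording, plus a smaller subset and a less precise hazard ratio, as the power table shows. Data collection and the primary analysis do not change, provided that baseline leave status is recorded.

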### Intervention

All participants will receive conventional medical care according to the regional guidelines and best practices. This consists of a brief instruction in exercises and pharmacologic management with the use of analgesics and anti-inflammatory agents and/or contact with a physiotherapist. The study’s additional occupational medicine intervention will last 3 months and include: 1) an initial consultation with the OP; 2) a workplace visit, if required; 3) a consultation with a physiotherapist; 4) a weekly telephone interview the first month and every second week the following two months with focus on adherence to the intervention plan; 5) midway interview with the OP with focus on return to/retention at work; 6) after three months a session with the OP evaluating the workplace-oriented intervention and the physical activity and concluding with further guidance. The intervention is illustrated in Figure 2.

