#### The initial consultation with the OP

The aim of this consultation is to establish knowledge about the participant’s work situation and uncover opportunities to remove barriers for maintaining the participant in his job. A systematic interview will be performed and will comprise the following: 1) a detailed description of the participant’s daily work, including work function, work tasks, general work demand, work tasks that aggravate the back pain and organisational problems. 2) If there is a potential need for support for social problems such as job insecurity, advice will be given and registered. 3) Advice to the participant regarding actual level of physical activity will be given. The consultation takes approximately one hour and will result in an agreed intervention plan.

The intervention plan can include: 1) workplace visit; 2) advice concerning possibilities for more variation during the work day; 3) temporary or permanent ergonomic changes; 4) change of work tasks and job routines; 5) need for job training; 6) transfer to other job tasks; 7) rehabilitation or additional formal education; 8) a schedule for gradual return to work; 9) advice on avoiding work loads that aggravate the low back problems. If necessary this plan will be adjusted at the following telephone interviews. A short communication form is sent to the GP to prevent conflicting advice to the participant in the return to/retain at work process and, if necessary, the social authorities and employment exchange will be contacted.

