### Anticipated risks and benefits

All participants will receive usual standard care, and no treatment will be withheld to participants in this trial. Both allocation groups receive active treatments with previously demonstrated efficacy and no known iatrogenic effects. This trial may benefit individual participants, since occupational medicine intervention is not generally available for the majority of people with LBP. Participants will receive an intensive level of monitoring so that if any participants experience deterioration of their LBP it will be identified and they will be referred to appropriate care in collaboration with their GP. To date there are no reported harms or adverse effects related to MRI if the procedure follows the international and national guidelines [35]. The standing position G-scan may be associated with dizziness and eventually orthostatic syncope, due to the standing posture. This complication will be met by an external pneumatic compression system applied to the participant’s legs which substantially reduces these events [36]. Research clinicians, physiotherapists and other staff are instructed to report all potential adverse effects to the project coordinator ([name] or [name]).

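### Being additional to GP care does not justify leaving conventional back-pain care out of the costs: the incremental cost may be biased if use differs between arms

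*Protocol article*

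**What the plan says.** The economic paragraph in the Statistics section of the protocol article starts from a premise: "This study is testing an additional intervention to the treatment provided by the participants’ GP". It draws a conclusion from that premise: "therefore, the direct intervention costs included the costs of the workplace and our occupational medicine intervention". The other side of the balance follows: "This will be compared to the costs of production losses estimated by a price of production loss of a worker per day". The only further category is expressly outside health care: "Further direct non-health care costs will be included (such as pension expenses, loss of productivity, schooling and redeployment". No cost of GP visits, physiotherapy, other providers or analgesics under conventional care is named.

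The Intervention section gives conventional care to all participants and describes it in open terms: "This consists of a brief instruction in exercises and pharmacologic management with the use of analgesics and anti-inflammatory agents and/or contact with a physiotherapist". The Discussion says that positive results that also show cost-effectiveness could lead to a change in policy.

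**The concern.** The article states a rule on which costs count, together with the reason for it, and the reason is a non sequitur. An add-on design means that both arms may use conventional care. It does not mean that they use the same amount after randomisation. If the intervention replaces some back-related care, the listed items overstate its incremental cost. If it prompts more care, they understate it. Either error would pass into the cost-effectiveness conclusion on which the article rests a possible policy change.

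**Working it through.** **Inputs.** The document gives no unit price, cost per participant or figure for care use, so there is no stated result to reproduce. The check uses an accounting identity, then compares the relevant sections.

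**Identity.** Per participant, let C be the intervention plus workplace cost, and let U1 and U0 be the mean conventional-care cost in the intervention and control arms.

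- Incremental cost with conventional care counted: (C + U1) − U0 = C + (U1 − U0).
- Incremental cost from the listed items: C.
- Amount left out: U1 − U0.

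Production losses and costs outside health care enter both versions in the same way and do not change this difference.

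**Illustration (all values assumed).** Set C = 1 and let use in the intervention arm change by a proportion r, so that U1 = U0 × (1 + r). The incremental cost relative to C is then 1 + U0 × r.

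| U0 (as a multiple of C) | r = −30% | r = −10% | r = 0 | r = +10% | r = +30% |
|---|---|---|---|---|---|
| 0.25 | 0.925 | 0.975 | 1.00 | 1.025 | 1.075 |
| 0.5 | 0.85 | 0.95 | 1.00 | 1.05 | 1.15 |
| 1.0 | 0.70 | 0.90 | 1.00 | 1.10 | 1.30 |

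For example, U0 = 0.5 and r = −30% give 1 + 0.5 × (−0.30) = 0.85. The r = 0 column shows that the omission does no harm if use is equal.

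**Is a difference plausible?** Four places in the article bear on this.

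1. *Intervention*: conventional care is not fixed in amount and may or may not include a physiotherapist ("pharmacologic management with the use of analgesics and anti-inflammatory agents and/or contact with a physiotherapist").
2. *Intervention*, *Consultation with a physiotherapist* and *Telephone interview*: the intervention arm alone has a trial physiotherapist, who plans three 45-minute activity sessions a week and telephones weekly in the first month, then every 14 days for two months. This could replace physiotherapist contact under conventional care.
3. *Study settings and recruitment*: GPs are kept informed of the allocation and of the intervention plan, so the people who provide conventional care are not blinded.
4. *Three months consultation with the OP*: intervention participants are encouraged to keep seeing their usual primary care providers for conditions other than back pain. The wording is specific to that arm and leaves open whether back-related care moves to the trial team.

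These make U1 ≠ U0 plausible. None of them establishes it or gives its direction.

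**The case against.** The strongest reply is that the exclusion is inferred. The quoted sentence defines the direct costs of the intervention, and background GP care is not one of those. The Background section defers the economic analysis to a later stage, and a condensed article may leave resource-use items to a fuller economic plan. That would answer a complaint about missing detail. It does not rescue the stated reasoning, which moves from the add-on design to a cost list whose only further category is outside health care.

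The reply is also right that the mechanisms are possibilities. The trial physiotherapist plans self-administered activity, and no hands-on treatment is described. The GP form has a limited purpose, consistent advice about work: "A short communication form is sent to the GP to prevent conflicting advice to the participant". No treatment is withheld from either arm.

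A reader might infer more than the documents support, in four ways:

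- *That the incremental cost will be wrong.* The bias is zero if use is equal, and nothing shows that it differs.
- *That closer monitoring creates an arm difference in referral.* The Anticipated risks and benefits section says of participants who deteriorate that "they will be referred to appropriate care in collaboration with their GP", but this covers all trial participants and does not separate the arms.
- *That Table 1 proves care use is not collected.* The table is presented as the list of outcome assessments. It also has no row for intervention costs or for the DREAM register data, both of which the article says will be used. A missing row therefore proves nothing.
- *That the error can be put as a share of the 6-day difference in the sample size section.* That needs contact numbers and unit costs that the documents do not give.

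**Conclusion.** The point holds in a limited form. The stated reason does not justify leaving conventional back-pain care out of the incremental cost, which may be biased by U1 − U0, in either direction and by an unknown amount, if use differs between arms. Under the assumptions tabulated above, a 10% change in use moves the incremental cost by 2.5% to 10%, and a 30% change by 7.5% to 30%. These figures show sensitivity and do not estimate this trial's error. As the intervention cost is also unknown, they do not show that the cost-effectiveness conclusion would change.

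Only the later economic analysis is affected. The primary outcome, the randomised comparison of sick leave and the sample size stand as they are. This is a cheap improvement and not a flaw in the main result.

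**What to change.** - Remove the inference from the add-on design to a restricted cost list. Include in the incremental cost the low back pain care used after randomisation in both arms: GP visits, physiotherapy or other provider contacts, and analgesics.
- Collect it with a short item, identical in both arms, at the existing 6-month and 1-year visits.
- Tabulate use by arm, which also helps readers interpret the sick-leave result.
- Where data are missing because recruitment has already begun, run a sensitivity analysis over a stated range of between-arm differences in use that includes zero.

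The cost is a few extra questions and some analysis time. Recall will be imperfect, and because participants know their allocation, the recall error cannot be assumed equal in the two arms. Recruitment began in March 2014 and was ongoing at submission, so participants already past a visit will lack the new items, which is why the sensitivity analysis is needed.
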